				Less variability inter-examinator on e-assessments than on paper-based screening
Secondary objective	Research question	Outcome	Measures	Testable hypothesis
To compare feasibility of the multimodality biometry e-measurements?	Is the neuro-developmental e-assessments as or more feasible to children and health practitioners than paper-based screening?	Feasibility: % children in the study failing finishing the e-assessments	Qualitative: semi-structured interviews	Higher proportion of children and health practitioners will affirmatively respond to feasibility for the e-measurement
		% of health practitioners reporting that e-questionnaires and psychometric games are easy to navigate around on the tablet		
To validate the clinical relevance of multimodality biometrics	Are multimodal biometry e-measurements clinically relevant metrics for neurodevelopmental and mental health?	Match mobile EEG biomarkers for neurodevelopmental and mental health with multimodality biometrics	Quantitative: electroencephalographic (EEG) biomarkers of cognitive, emotional, and behavioral performance in children aged 7–12 years	Compare EEG signals obtained while children are playing with biometrics measurements related to well-characterized EEG signatures for related mental health in children (P2, N170, P300 amplitude and latence, Ratio Theta/Beta (TBR), Frontal Theta and Delta Power, Posterior Alpha et beta Power)
To determine factors associated with level of disclosure of symptoms related to neurodevelopmental and mental health	What factors are associated with risk of neurodevelopmental and mental health?	Identification of factors that significantly increase odds of neurodevelopmental and mental health reported symptoms	Quantitative: (1) demographic variables (age, gender, SES), (2) medical status (current NDD status, history), (3) psychopathological scores and quality of life (BRIEF, CBCL, ADHD scale, ASQ-10, PSQI, Grit questionnaire, SMQ)	Compared to paper-based screening, e-screening promotes greater disclosure
To determine multimodality biometric e-assessment as a monitoring tool		Examination of significant changes of either or both scores compared with baseline (repeated testing)	Quantitative: compared 4-month follow-up scores of e-assessment and paper-based screening with those obtained at baseline	More variability of scoring in those obtained from paper-based screening will be expected than those from e-assessment

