### Questionnaires and neuro-assessments

All questionnaires and neuro-assessments are summarized in Table 4. At baseline and T2-end, the visit will be conducted in a sequential manner with breaks. First, children will perform neuropsychological assessments through digitalized or paper/pencil WISC-V battery [1.5 h, (50)] with the Similarities, Vocabulary, Coding, Symbol search, Block design, Digit, Matrix reasoning subtests. Secondly, questionnaires will be answered digitally for:

▪ Demographic information (age, gender, language spoken, family structure, school, previous diagnosis for neurodevelopmental disorder) and scoring of manual laterality [Edinburgh handedness, short version, 4 items (54), estimated intellectual quotient (50), and sleep quality (Pittsburgh Sleep Quality Index, 11 items) (55)].▪ The French version of the ADHD-Rating Scale (56) incorporating the 18 criteria rating Inattention (sum of odd items scores) and Hyperactivity-Impulsivity (sum of even items scores) symptoms.▪ The French version of the Children Behavior Check List [short version, 32 items, (57) and Conners-3 (58)—psychopathological behavioral or emotional traits].▪ The Autism Quotient List French version scoring [10 items, (59)]—psychopathological behavioral or emotional traits.▪ The Developmental Coordination Disorder Questionnaire [DCDQ, 15 items, (60)].▪ The Behavioral assessment of executive function scoring [BRIEF, 72 items, (61)].▪ The French versions of the School Motivation Questionnaire [SMQ, 44 items, (62)] and the Grit-Scale for Children and Adult [GSCA, 12 items, (63)].

**Table 4 tab4:** Explanatory variables for the XAI4Kids^®^ e-measurement tool.

Neuropsychologic tests	Variables
	Reaction time: average reaction time (RT) for every executed task
	Hits: number of correct answers
	Total errors: total number of errors
	Wrong answers: number of answers that are not omission, perseverance and outliers
	Omission: reaction time = 0 ms
	Distractors: number of answers looking similar to the target answer
	Persévérance: 0 ms < reaction time < 100 ms
	Outliers: standard deviation of reaction time (exécution) < 3 x standard deviation (si RT≠0)
	Hits RT: median of reaction time for correct answers
	Hits RT SE: standard error de Hits RT
	SE variability: standard deviation of the 3 standard errors calculated for each task block (mesure of the participant variability)
	Hits rt block change: slope change for RT between blocks (vigilance)

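### The hypothesis that e-screening brings greater symptom disclosure than paper cannot be tested, because no symptom questionnaire is given on paper; the same Table 1 row does not separate outcome from factors.

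*Protocol article*

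**What the plan says.** In Table 1, the disclosure row has four entries that matter here.

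- Objective: "To determine factors associated with level of disclosure of symptoms related to neurodevelopmental and mental health".
- Outcome: "Identification of factors that significantly increase odds of neurodevelopmental and mental health reported symptoms".
- Measures, one numbered list: "1) demographic variables (age, gender, SES), (2) medical status (current NDD status, history", followed by item (3), "psychopathological scores and quality of life (BRIEF, CBCL, ADHD scale, ASQ-10, PSQI, Grit questionnaire, SMQ".
- Hypothesis: "Compared to paper-based screening, e-screening promotes greater disclosure".

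On how the questionnaires are completed, the section Questionnaires and neuro-assessments describes the visits at baseline and at the end of follow-up. Children first take the WISC-V, digitally or with paper and pencil. Then: "Secondly, questionnaires will be answered digitally for", and a list of instruments follows. The Abstract (Methods and analysis) agrees that families complete the demographic, psychosocial and health assessments online. Study design calls the study observational and uncontrolled.

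**The concern.** Disclosure is what a parent or child is willing to report. To claim that one mode brings out more of it than another, the study needs symptom reports in both modes, from the same families or from comparable groups. The article sets up only the electronic mode. If the hypothesis stays in the list, the study will be expected to report on a contrast for which it holds no comparator. Any statement about paper would then rest on something outside the data. The Introduction itself warns that some tools behave differently when delivered online, so equivalence with published paper results cannot be assumed.

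A second, smaller problem lies in the same row. It asks which factors raise the odds of reported symptoms, but it names no scale as the record of those symptoms. The only symptom scales in the row stand in the same numbered list as the demographic and medical variables. A reader cannot tell what goes on which side of the model.

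**Working it through.** The plan gives no effect size, power or sample size for this objective, so there is no figure to reproduce. The check is to trace each scale to its mode, and then to read the columns of the row against each other.

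**Step 1. Mode of each scale in item (3).**

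| Scale in Table 1 | In the digital list of Questionnaires and neuro-assessments? | Paper version described? |
|---|---|---|
| BRIEF | yes | no |
| CBCL | yes | no |
| ADHD scale | yes | no |
| ASQ-10 (10-item autism list) | yes | no |
| PSQI | yes | no |
| Grit | yes | no |
| SMQ | yes | no |

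So 7 of 7 are digital and 0 of 7 have a paper version. The DCDQ and Conners-3, the other symptom questionnaires in that section, are in the same digital list.

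**Step 2. Other possible sources of a paper symptom report.**

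- WISC-V: may be paper/pencil, but it measures performance. Nobody reports a symptom on it.
- Semi-structured interviews: the legend of Figure 2 gives their content as background, demographics and medical history. Table 1 uses them for acceptability and feasibility.
- Follow-up visit: described with the same digital questionnaires as baseline, so the repeat assessment adds no paper arm.
- Allocation to mode: none described.

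With no paper symptom reports, a difference or odds ratio of electronic versus paper has one empty side and cannot be estimated.

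**Step 3. Outcome and factors in the row.** There are two readings.

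- Item (3) is the outcome, and items (1) and (2) are the factors. Nothing is circular, although sleep, perseverance and school motivation fit poorly as neurodevelopmental symptoms.
- Item (3) is a third group of factors, parallel to (1) and (2). The row then has no measure of reported symptoms except those same scales, and symptoms would be explained by themselves.

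The row does not choose. Its objective concerns disclosure, its research question concerns risk ("What factors are associated with risk of neurodevelopmental and mental health") and its hypothesis concerns mode. These are three different quantities.

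**Step 4. Illustration for the second reading only.** Assume that two scales are bivariate standard normal with correlation ρ, that the outcome is being in the top 15% on the first, and that the predictor is the second. With c the 85th percentile of the standard normal and Φ its distribution function, the chance of the outcome given x is Φ((ρx − c)/√(1 − ρ²)). The best-fitting logistic slope gives these odds ratios per SD:

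| Assumed ρ | Odds ratio per SD |
|---|---|
| 0.3 | about 1.8 |
| 0.5 | about 2.8 |
| 0.6 | about 3.9 |
| 0.7 | about 5.9 |

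Neither the correlations nor the cutoff come from the article. The table shows only that overlap between symptom scales could by itself produce sizeable associations.

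**The case against.** **Paper-based screening may not mean a paper copy of each questionnaire.** Elsewhere in Table 1 the phrase stands for the conventional battery as opposed to the games. This is a fair reading of the term, but it does not rescue the hypothesis. The variables listed for the tool in Table 4 are reaction times, errors and tracking measures. They are not symptoms that someone chooses to report, so a battery-versus-games comparison would have no disclosure on the electronic side.

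**Paper questionnaires may exist without being described.** The digital list omits two instruments in Table 2 (a child sleep questionnaire and a brain-injury screen), and the data section mentions stored paper/pencil files. The files are explained by the WISC-V. The two omitted instruments are not among the seven scales of this row. It would be too strong to say that every form in the study is digital; for the scales that matter here, the text is clear.

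**A reader might infer that the plan uses the symptom scales on both sides of the model.** The article does not say so. The scales stand under Measures, a column that elsewhere in the table often gives the data source of the outcome. The row is ambiguous, not shown to be circular. The DCDQ and Conners-3 could also supply an outcome from outside the row.

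**A reader might infer that current NDD status must leave the factors.** That does not follow. For a question about disclosure, known diagnosis is a natural covariate, because without it low disclosure cannot be told apart from absence of symptoms. The sample deliberately mixes diagnosed and typically developing children.

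**Detail is left to the full protocol or SAP.** This holds for cutoffs and the final covariate set. It does not hold for a hypothesis that contradicts the stated data collection.

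**Conclusion.** The mode hypothesis is wrong as written. Table 1 promises an electronic-versus-paper contrast in disclosure, while the Abstract and the methods describe electronic symptom reporting only: 7 of 7 listed scales are digital and none has a paper counterpart. This rests on taking disclosure to mean the reporting of symptoms by children or parents, as the row's own outcome does.

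The lack of separation between outcome and factors is a real ambiguity in the same row and should be settled in the same edit. It is not evidence of a circular analysis, and the odds ratios above are not predictions for this study.

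The consequence is limited to one secondary hypothesis. What changes is what the study may conclude: it can describe symptoms reported electronically and what goes with them, but not whether the electronic mode raised reporting.

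**What to change.** In the disclosure row of Table 1:

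1. Delete the greater-disclosure hypothesis, or replace it with a descriptive aim: to describe symptoms reported electronically and the factors associated with them. State that no effect of mode will be claimed.
2. Name the scale or scales that form the reported-symptom outcome, and do not use those same scales as explanatory factors. Current NDD status may stay as a covariate.
3. Align the objective, the research question and the outcome on one quantity.

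The cost is wording, and one secondary hypothesis is given up. If the sponsor wants to keep the hypothesis, the design has to change: the same questionnaires would also have to be given on paper, with mode or order randomised. That is a larger change, with added burden for families, and the descriptive aim does not need it.

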### Primary objective

The primary objective of the study is to determine whether a normative base relying on multimodality biometry e-measurements tool, called XAI4Kids®, can evaluate brain functioning, i.e., the psychometric properties (sensitivity, specificity, reliability, reproducibility, and positive/negative predictive values) in children aged 7 to 12 years and evaluate the efficiency and acceptability of such e-screening tool compared to various current convergent validity measures of brain functioning (Figure 2).

#### The multimodality biometry tool description

The XAI4Kids® Multimodality Biometry tool has been developed by O-Kidia, SAS, and is composed of several technological components (Tables 2
3):

▪ The unmodified tablet: data will be collected in ecological context during the session to minimize stigma. Participant’s main biometry parameters (e.g., eye-, face-, and digit-tracking, frequencies, etc.), clicking, taping, and video from the intrinsic camera will be recorded to reflect of the child’s performances.▪ The O-Games: a series of gamified psychometric sessions, which will engage the participants to perform as the best, and stimulate the cognitive, emotional, and behavioral functions of each participant. Games were developed for Android with Unity^1^ and will be installed on each participant’s table.

**Table 2 tab2:** Study workflow at baseline.

Name	Description	Time	Who	Visit
Screening worksheet	Eligibility criteria	10 min	Y, P	B
Modified Ohio State TBI Screen-Short Ver	TBI rule-outs at BL; TBI	5 min	P	B
Demographics domain	demographics, race, gender, family structure, SES	20 min	P	B
Medications	Medical history, medications	5 min	P	B
Pittsburgh Sleep Quality Index	Sleep habits	5 min	P	B, T2-end
Children’s Sleep Habits Questionnaire	Sleep habits	5 min	Y	B, T2-end
Questionnaires for parent	ADHD-rating scale, Children Behavior Check, BRIEF, DCDQ, Conners 3	20 min	P	B, T2-end
Questionnaires for child	ADHD-rating scale, ASQ-scale, Grit scale, and SMQ	20 min	Y	B, T2-end
WISC-V (substest)	7 subtests Symbol, Cubes, Code, Comprehension, Letter-Number sequences, matrix, and similitude	45 min	Y	B, T2-end
O-Games battery	5 psychometric games	20–35 min	Y	B, T2-end
Breaks	As much as needed	20 min	Y	B, T2-end

**Table 3 tab3:** Convergent validity measures for the XAI4Kids^®^ e-measurement tool.

What it measures	Stream data type	Convergent validity measures
Visio-spatial processing	Rocket	WISC-V, block design
	SES4ME	WISC-V, symbol search
	O-TOM	WISC-V, barrage
Working memory	Untangle, EEG (P3b)	WISC-V, letter-number sequences
Episodic memory	O-G	WISC-V, letter-number sequences, digit-span
Attention	Rocket, connect	WISC-V, digit span, coding, symbol search
Speed processing	Connect	WISC-V, symbol search (immediate recall) coding
Language	O-KIDO	WISC-V, comprehension, vocabulary,
Executive functions	O-MAZE	WISC-V, BRIEF, vocabulary,
Auditive Attention	O-METRO	WISC-V, digit span
Anxiety	EEG and video-analysis	CBCL subtest
Sleep	EEG and video-analysis	PSQI
Motivation	EEG and video-analysis	SMQ, grit scale
Emotional control	EEG and video-analysis	BRIEF
Social abilities	O-TOM, EEG, and video-analysis	CBCL subtest, ASQ
Visual motricity	Eye-tracking	WISC-V, symbol search, coding
Visual acuity	Eye-tracking	WISC-V, symbol search

In addition, the tool is constituted by:

▪ The AI module: the backend part of XAI4Kids® system will allow the clinical recommendations of biometry extracted features (43–48) based on machine and deep learning algorithms. Data-driven coefficients from first-level analyses for each participant will be provided for each analysis. To facilitate Big Data deployment, and re-use, the computational workflows will be implemented as virtual machines (VMs), deployable on multiple computing resource and on local workstations. Each metric will be obtained from time-series data and stored in the time-series analysis database. The query object graph analysis method will be used to enable analysis sharing among analysts by preventing duplicate processing and data explosion (49).▪ The artificial setting: to extract features of interest from the signals, tracking software and algorithms have been specially developed for feature extractions.

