### Participant

The inclusion criteria will be: (i) boys or girls of any ethnicity, aged 7–12 years (typically developing and diagnosed with NDDs); (ii) French native speakers; (iii) normal hearings, normal or corrected-normal vision; (iv) no brain trauma; (v) an estimated intelligence quotient of 85 and above (exclusion if score < 25th percentile) based on Weschler’s subtests Matrix Reasoning and Similarities (50); (vi) no history of co-morbid psychiatric illness that might confound the analysis of the study (e.g., schizophrenia, obsessive-compulsive disorder, major depression, or bipolar disorder); (vii) ADHD medications and Selective serotonin reuptake inhibitors (SSRIs) are not exclusionary since use of these medications is associated with neurodevelopmental disorder condition, but the treatment will be suspended 2 days before any cognitive evaluation.

The exclusion criteria will be: (i) failure to meet the inclusion criteria; (ii) lack of written informed consent: the child and at least one of the parents (or the legal representative) must sign the informed consent form.

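### Treatment status is scheduled for recording at baseline only, so at retest a child whose treatment changed cannot be told apart from a child whose score is unstable

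*Protocol article*

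**What the plan says.** **What is recorded when.** Table 2 (study workflow) has a Visit column that separates baseline (B) from baseline plus follow-up (B, T2-end). The Medications row ("Medical history, medications") and the head-injury screen ("TBI rule-outs at BL; TBI") are coded B. The O-Games battery ("5 psychometric games"), the WISC-V subtests, the parent and child questionnaires and both sleep scales are coded B, T2-end.

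**What the repeat scores are for.** In Table 1, the monitoring-tool objective gives its measure as "compared 4-month follow-up scores of e-assessment and paper-based screening with those obtained at baseline". Its hypothesis is: "More variability of scoring in those obtained from paper-based screening will be expected than those from e-assessment".

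**Who may be treated.** Under Participant, criterion (vii) states that "ADHD medications and Selective serotonin reuptake inhibitors (SSRIs) are not exclusionary", and adds that "the treatment will be suspended 2 days before any cognitive evaluation". Under Recruitment, outpatient clinics and physician referrals are among the sources.

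**Model.** The hypothesis testing framework centres on interactions with time. It names age and gender as covariates, leaves other background variables open, and names no treatment variable measured at follow-up.

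**The concern.** A monitoring tool has to separate real change in the child from noise in the measurement. The retest comparison can do that only if the analyst knows which children had a reason to change. Starting, stopping or changing a treatment is such a reason. It is foreseeable here, because diagnosed and treated children are eligible and some come from clinics.

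With treatment status scheduled at baseline only, any treatment-related shift enters the retest difference unlabelled. Two readings are at stake:

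- the mean change from baseline;
- the comparison of score variability between the conventional and the tablet measures.

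The second is the more delicate. The two kinds of measure are taken in the same child, so a real change that moves both equally leaves the contrast roughly alone. A change that moves one more than the other makes that one look less stable. Suspension before cognitive evaluations is the kind of rule that could produce such an imbalance, since it names cognitive evaluations and not behaviour questionnaires.

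**Working it through.** **1. The schedule.** Of the 11 rows in Table 2, four are coded B only: screening worksheet, head-injury screen, demographics and medications. The other seven, including breaks, are coded B, T2-end. The table is titled as a baseline workflow, but its Visit column also schedules the follow-up visit, so the B code on the Medications row is a stated choice.

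**2. Is treatment status captured at T2-end elsewhere?**

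- *Study design* mentions a semi-structured interview and the Figure 2 legend links interviews to medical history. Neither gives a follow-up timing or medication content.
- *Questionnaires and neuro-assessments* describes the visit at baseline and T2-end and lists demographic information and previous diagnoses, but not medication.
- *Safety and adverse event assessment* provides for event reporting, which might pick up a head injury but not a routine treatment change.

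No section states a T2-end treatment record.

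**3. Size.** The plan has no figure of its own to reproduce on this point: it gives no rate of treatment change, no effect and no retest correlation. All three inputs below are assumptions.

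- r, retest correlation: 0.8 (range 0.7-0.9)
- p, share of retested children whose treatment changes: 5-20%
- d, shift in their score: 0.3-0.8 SD, all in one direction

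Formulas, in units of the score SD:

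- variance of change with no treatment effect = 2(1 - r); at r = 0.8 this is 0.40
- shift in mean change = p × d
- added variance = p(1 - p)d²

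Results at r = 0.8:

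| p | d | Mean shift (SD) | Added variance | Rise in variance of change |
|---|---|---|---|---|
| 5% | 0.3 | 0.015 | 0.0043 | 1.1% |
| 10% | 0.5 | 0.05 | 0.0225 | 5.6% |
| 10% | 0.8 | 0.08 | 0.0576 | 14.4% |
| 20% | 0.8 | 0.16 | 0.1024 | 25.6% |

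The mean shift does not depend on r. Over r = 0.7 to 0.9 the rise in variance runs from 0.7% to 51%.

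**4. Direction of shifts.** If equal numbers shift up and down, the mean shift is 0. The variance is still inflated: at p = 10%, d = 0.8, r = 0.8 the added variance is 0.10 × 0.64 = 0.064, or 16% of 0.40.

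**5. The variability contrast.** With equal r, the difference in added variance between two measures is p(1 - p)(d₁² - d₂²). If both respond equally, it is 0. Suppose suspension removes the effect on the games (d₂ = 0) and a questionnaire keeps d₁ = 0.5. At p = 10%, r = 0.8, the questionnaire's variance of change is then 5.6% larger for a reason unrelated to measurement quality. Which side of the contrast this favours is not certain. Table 3 lists questionnaires among the comparators, while the methods text says they are answered digitally.

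**6. How many children.** 10% of 400 is 40, of 543 about 54, of 786 about 79. At p = 10%, 40 retested children include about 4 changers. The Figure 1 legend instead expects about 500 at the 2-month follow-up. The interval is 2 months in Study design and Figure 1, and 4 months in Table 1.

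**The case against.** **The table may not be the whole collection plan.** A condensed article with no case report form cannot prove that nothing is asked at T2-end. Table 2 also codes demographics B only, whereas the text lists them for a visit described as occurring at both time points. This stands as a limit: a reader might infer that adjustment is impossible, and the article does not establish that. It does establish that the stated schedule omits the item.

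**The suspension rule already deals with it.** The WISC-V and games are planned off ADHD drugs and SSRIs at both visits, and applying the rule at T2-end requires staff to ask about treatment. This stands in part. It reduces the likely effect on cognitive scores, but the rule names only those drugs and does not clearly reach the questionnaires. The article also states no record of who was treated or suspended at T2-end.

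**It inflates false positives.** A reader might go further and say that the chance of declaring change when there is none more than doubles. With n = 40, p = 10%, d = 0.8 and r = 0.8, a two-sided 5% test of mean change does reject about 11% of the time. The documents do not support that reading:

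- Nothing in them supplies d; at d = 0.5 the figure is about 7.6%.
- It assumes every shift goes one way. A 75/25 split at d = 0.8 gives about 6.5%, and an even split gives 5.0%.
- It ignores the suspension rule.
- The modelled children have truly changed, so this is misattribution and not a type I error.
- It concerns a one-sample mean, while the stated hypothesis compares variability between methods.

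**It is a small matter.** One secondary objective in a retest subsample is affected, and the baseline normative work is untouched. That is right, and head injury over a few months should be rare.

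**Conclusion.** The point holds in a limited form. The stated schedule repeats every score-producing assessment at T2-end but not the treatment record. A child whose treatment changed between visits therefore cannot be told apart, on the scheduled data, from one whose score is unstable. The variability comparison between conventional and tablet measures could be affected unequally, because suspension applies to cognitive evaluations and not clearly to questionnaires.

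The size is unknown and probably modest. Under the assumed 5-20% changing treatment and 0.3-0.8 SD shifts in one direction, the mean change moves by 0.015-0.16 SD. Shifts in both directions reduce this, and so does effective suspension. Opposing shifts do not remove the added variance. The head-injury part is minor. The primary baseline analysis does not depend on this point.

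**What to change.** - In Table 2, change the Medications row from B to B, T2-end. As a minor addition, do the same for the head-injury screen, asked as an interval-injury question.
- Report retest change and variability for both methods twice: in all retested children, and without those whose treatment status changed or who had an interval head injury. This sensitivity analysis is preferable to a covariate, which about 4 changers in 40 would estimate very imprecisely.
- Reconcile the follow-up interval (2 months in Study design, 4 months in Table 1) and the retest number (10% in Study design, about 500 in the Figure 1 legend). They determine how much treatment change is possible and how many families are affected.

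**Cost.** Two existing 5-minute parent forms, about 10 minutes per retested family, and one sensitivity analysis. With a 10% subsample that is about 40 to 79 families; if the figure of about 500 is the intended one, the burden grows in proportion. No treatment rule needs to change.
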